#### Module 2. standardization of antibiotic initiation criteria for EOS

2.6.2

To minimize inter-center and inter-physician variability in EOS management, a unified *EOS Risk Assessment and Antibiotic Management Clinical Pathway* (Figure 2) was developed based on nationally published evidence-based recommendations in China (23) and will be mandatorily implemented across all participating NICUs. This pathway translates complex clinical decision-making into a stepwise, standardized workflow. Core assessment domains include the following:

**Figure 2 F2:**
[figure not shown]
Standardized clinical pathway for risk assessment and antibiotic management of suspected early-onset sepsis. 1. Suspected intra-amniotic infection: Defined as maternal intrapartum fever (temperature ≥39.0 °C or 38.0 °C−38.9 °C persisting for >30 min) accompanied by one or more of the following clinical signs: (1) maternal leukocytosis (>15 × 10^9^/L); (2) purulent cervical discharge; (3) fetal tachycardia (>160 beats/min) persisting for 10 min or longer; (4) cloudy or foul-smelling amniotic fluid. 2. Confirmed intra-amniotic infection: defined as maternal intrapartum fever (temperature ≥39.0 °C or 38.0 °C−38.9 °C persisting for >30 min) accompanied by one or more of the following positive laboratory findings: (1) positive Gram stain of amniotic fluid; (2) positive amniotic fluid culture; (3) histopathological evidence of inflammation or infection in the umbilical cord, placenta, or fetal membranes. 3. Preterm infants at high risk for infection: defined as: (1) Infants with gestational age ≥35 weeks and ≥1 perinatal risk factor(s): ① intra-amniotic infection (confirmed or suspected); ② PROM ≥18 h. (2) Infants with gestational age < 35 weeks and ≥1 perinatal risk factor(s): ① intra-amniotic infection (confirmed or suspected); ② preterm birth caused by PROM. GBS, group B streptococcus; PROM, premature rupture of membranes; CBC, complete blood count; CRP, C-reactive protein.

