**1) Maternal perinatal infection risk factors**

Including, but not limited to:

Suspected or confirmed intra-amniotic infection (definitions provided in the Figure 2 legend) (24);Prolonged rupture of membranes ≥18 h;Spontaneous preterm birth or preterm birth of unclear etiology;Maternal Group B Streptococcus colonization or bacteriuria;Isolated intrapartum maternal fever.

These factors are considered to increase EOS risk but do not independently constitute absolute indications for empirical antibiotic therapy.

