**2) High-risk preterm infants and neonatal clinical presentation**

A distinction is made between high-risk preterm infants and non-specific clinical signs:

High-risk preterm infants constitute an indication for initiating antibiotic therapy (definitions provided in the Figure 2 legend) (23);Severe abnormal clinical manifestations (e.g., septic shock, requirement for cardiopulmonary resuscitation, need for invasive mechanical ventilation within the first 3 days of life or following clinical deterioration, severe apnea) are considered absolute indications for antibiotic initiation;Other nonspecific clinical abnormalities require integrated assessment incorporating perinatal risk factors and laboratory findings.

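### The Figure 2 legend gives its high-risk preterm group an arm from 35 weeks with no upper limit, so it is unclear whether a term infant with one listed factor has an indication for antibiotics

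*Protocol article*

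**What the plan says.** Three places in section 2.6.2 (Module 2) of the Protocol article bear on this.

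- **Figure 2 legend, item 3.** The group is introduced as "Preterm infants at high risk for infection: defined as: (1) Infants with gestational age ≥35 weeks and ≥1 perinatal risk factor(s". The factors for this first arm are "① intra-amniotic infection (confirmed or suspected); ② PROM ≥18 h". A second arm covers "Infants with gestational age < 35 weeks and ≥1 perinatal risk factor(s", where the factors are intra-amniotic infection or preterm birth due to rupture of membranes.
- **Part 1), maternal risk factors.** The list includes "Suspected or confirmed intra-amniotic infection (definitions provided in the Figure 2 legend" and "Prolonged rupture of membranes ≥18 h", and closes with: "These factors are considered to increase EOS risk but do not independently constitute absolute indications for empirical antibiotic therapy".
- **Part 2), high-risk preterm infants and clinical presentation.** It states: "High-risk preterm infants constitute an indication for initiating antibiotic therapy (definitions provided in the Figure 2 legend". The term *absolute indication* is kept for severe clinical manifestations. Other nonspecific clinical abnormalities are to be assessed together with risk factors and laboratory results.

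The pathway is mandatory in all participating units and is meant to reduce variation between centres and physicians. Section 2.5 names the lack of standard initiation criteria as a driver of overuse.

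**The concern.** The legend's label and its criterion do not match. A group called preterm has an arm that starts at 35 weeks and has no stated end. Part 2) sends the reader to the legend for the definition, so the legend decides who has an indication.

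Two careful readers can therefore reach different initiation decisions for the same term infant. Part 1) does not help them choose. It plays down the same two factors, but in a term (*absolute indication*) whose practical difference from *indication* is never explained.

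Initiation decisions feed the antibiotic use rate, a primary outcome (section 2.7.1). The intervention adherence rate (section 2.7.3) counts whether the initiation assessment and the 48–72-h reassessment were completed as the protocol specifies. If the specification can be read in two ways, units using either reading can be scored adherent, and deviation review has no single standard to work from.

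**Working it through.** The article gives no figure to reproduce on this point. The check is a comparison of wording.

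**1. Literal reading of the legend.** The first arm takes every infant of 35 weeks or more and the second takes every infant below 35 weeks, so together they cover all gestational ages. Intra-amniotic infection alone then places any infant in the group, and membrane rupture of at least 18 h alone does so for any infant of 35 weeks or more. The word preterm excludes nobody.

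**2. Reading governed by the heading.** The first arm covers only preterm infants of 35 weeks or more. The indication is then prematurity plus a factor. The factor is not acting independently, so part 1) is respected. The upper limit is implied by the heading but not written.

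**3. Where the two readings differ** (infants without severe manifestations):

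| Infant | Literal reading | Heading reading |
|---|---|---|
| Below 35 weeks, with a second-arm factor | In the group: indication | In the group: indication |
| Preterm, 35 weeks or more, with one first-arm factor | In the group: indication | In the group: indication |
| Term, with one first-arm factor | In the group: indication | Outside the group: risk factor only |

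Only the last row differs. Only two factors can produce it: maternal Group B Streptococcus colonization, isolated intrapartum fever and spontaneous preterm birth do not trigger the first arm.

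**4. Part 1) against part 2).** Part 1) denies that the factors are independently *absolute* indications. Part 2) calls the group *an indication*, without that adjective. The two statements can both be true if the terms differ, but the article does not say what a clinician does differently under each.

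**5. Size.** Table 1 gives 862 + 524 + 395 + 872 + 484 = 3,137 annual admissions in 2024. The number affected would be 3,137 × (share born at term) × (share of those with one listed factor as their only criterion). The article gives neither share, so the number cannot be computed. As a conversion only: each 1% of admissions in the disputed row is 3,137 × 0.01 ≈ 31 infants a year. That is at most 1 percentage point of the antibiotic use rate, reached only if every such infant's treatment turned on the reading.

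**The case against.** The strongest reply is that the heading already supplies the missing limit. Item 3 says preterm, part 2) repeats it, and a reading that empties the word of meaning is the weaker one. With the heading in force, most of the tension with part 1) disappears. This is a fair reading, but the criterion as written does not impose it, and the criterion is what a clinician filling in a form would apply.

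A reader might infer more than the article supports in four ways:

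- **A flat contradiction between parts 1) and 2).** Part 1) denies only an absolute indication, so the two are not strictly opposed. Nor does part 1) call for integrated assessment of these infants; part 2) asks for that in the case of nonspecific clinical abnormalities.
- **That centres will act in opposite ways.** The flowchart is not available here and may route term and preterm infants separately. One steering committee sets standards and training, and flagged deviations are reviewed monthly across centres (section 2.6.1). These controls make lasting, unnoticed divergence less likely, though they do not correct the text.
- **A definite count of affected infants.** That would need gestational-age and risk-factor shares that the article does not give.
- **That the time-series estimate is invalid.** The analysis estimates the effect of the whole bundle, and this ambiguity does not undo that.

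What remains is that part 2) names the legend as the source of the definition. The legend therefore needs correcting even if the flowchart is clear.

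**Conclusion.** The point holds as a defect in one stated initiation criterion of the mandatory pathway. The legend's label and its open-ended arm give different answers for term infants with one of two factors, and the article leaves *indication* and *absolute indication* undistinguished. Different practice between centres is possible, not demonstrated, and the number of infants cannot be derived from the document.

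Severity is moderate. The matter touches a primary outcome, and the adherence measure might not reveal it, but it is a wording inconsistency that the unseen flowchart may already resolve. This conclusion rests on the legend and text alone and takes no position on which clinical rule is right.

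**What to change.** The investigators should reconcile item 3 of the Figure 2 legend with parts 1) and 2) of section 2.6.2, and check that the flowchart and the standardized form agree with the result. The reconciled text should state:

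- the gestational-age range that the high-risk preterm group covers, with both ends written;
- whether a single listed factor within that range is an indication;
- what separates an *indication* from an *absolute indication* in action.

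One text should go to all five centres, and pathway adherence and deviations should be judged against it. If the clarification is made during the intervention period (April 2026 to March 2027), its date should be recorded so that it can be marked on the control charts and in the time series.

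The cost is a wording correction to the pathway and form and a notice to the centres. No new data are needed.

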**1) Maternal perinatal infection risk factors**

Including, but not limited to:

Suspected or confirmed intra-amniotic infection (definitions provided in the Figure 2 legend) (24);Prolonged rupture of membranes ≥18 h;Spontaneous preterm birth or preterm birth of unclear etiology;Maternal Group B Streptococcus colonization or bacteriuria;Isolated intrapartum maternal fever.

These factors are considered to increase EOS risk but do not independently constitute absolute indications for empirical antibiotic therapy.

**2) High-risk preterm infants and neonatal clinical presentation**

A distinction is made between high-risk preterm infants and non-specific clinical signs:

High-risk preterm infants constitute an indication for initiating antibiotic therapy (definitions provided in the Figure 2 legend) (23);Severe abnormal clinical manifestations (e.g., septic shock, requirement for cardiopulmonary resuscitation, need for invasive mechanical ventilation within the first 3 days of life or following clinical deterioration, severe apnea) are considered absolute indications for antibiotic initiation;Other nonspecific clinical abnormalities require integrated assessment incorporating perinatal risk factors and laboratory findings.

**3) Laboratory findings**

Non-specific laboratory markers (WBC count, I/T ratio, CRP, PCT, PLT) are used as adjunctive tools. Abnormality in a single parameter alone does not constitute sufficient justification for initiating or prolonging antibiotic therapy. Definitions of laboratory positivity are provided in Supplementary Table S1 (Supplemental material 1).

The pathway will be embedded into routine workflows as a standardized form. Documentation will be mandatory for all empirical antibiotic initiations. Deviations from pathway recommendations require explicit documentation of clinical justification in the medical record. Pathway adherence is monitored as a core process indicator and incorporated into monthly quality feedback and Plan-Do-Study-Act (PDSA) cycles.

#### Module 3. Mandatory 48–72-h antibiotic reassessment

2.6.3

All neonates receiving antibiotics undergo mandatory reassessment at 48–72 h, covering:

Changes in clinical status;Microbiological test results;Dynamic trends in nonspecific laboratory markers.

Based on reassessment findings, clinicians must select one of the following actions:

Discontinue antibiotics;Modify or de-escalate the antibiotic regimen;Continue therapy with explicit documentation of clinical justification.

For neonates with suspected EOS in whom the diagnosis is excluded within 48–72 h, discontinuation of antibiotics is mandatory (see Figure 2). All antibiotic-treated neonates must complete reassessment and a documented treatment decision within the 48–72-h window. Failure to complete reassessment is classified as a protocol deviation and is identified during monthly audits and targeted for subsequent improvement efforts. Diagnostic criteria for EOS and LOS are provided in Supplementary Table S2 (Supplementary material 1).

#### Module 4. Standardization of empirical antibiotic regimens

2.6.4

During the intervention period, empirical antibiotic prescribing follows unified principles across centers:

EOS: ampicillin (or penicillin) in combination with a third-generation cephalosporin;Community-acquired LOS: preferential monotherapy with a third-generation cephalosporin;Hospital-acquired LOS: selection guided by local microbiological profiles and resistance patterns, with preference for narrow-spectrum combination regimens.

Once pathogen identification and susceptibility results become available, antibiotic therapy is promptly narrowed to targeted, susceptible agents, with monotherapy preferred whenever feasible.

#### Module 5. Staff education and decision support

2.6.5

During both the preparation and intervention phases, targeted educational sessions, visual workflow displays, and concise decision-support materials are provided to enhance NICU healthcare workers' awareness of appropriate antibiotic use and the goals of the QI initiative.

#### Module 6. Continuous monitoring and adaptive optimization using PDSA cycles

2.6.6

To ensure consistent implementation across multiple centers and enable dynamic optimization based on real-time feedback, a structured “monitor–feedback–improve” loop is established. Rapid PDSA cycles are embedded within the two-tier governance structure to drive continuous QI.

PDSA cycles are integrated into the monthly multicenter collaborative meetings as follows:

Plan: During each monthly meeting convened by the regional steering committee, 1–2 high-priority, actionable problems (e.g., delayed antibiotic discontinuation) are identified based on data review, and targeted improvement plans are formulated;Do: Hospital-level implementation teams execute the improvement plan within their NICUs over the subsequent monthly cycle;Study: Relevant process data (e.g., audit records for antibiotic courses exceeding 72 h) are collected and reported at the next collaborative meeting, with cross-center comparison;Act: The steering committee and participating centers jointly evaluate effectiveness. Successful practices are incorporated into standardized operating procedures and disseminated across all centers; ineffective strategies are revised, and a subsequent PDSA cycle is initiated.

### Outcomes

2.7

#### Primary outcomes

2.7.1

Antibiotic use rate: the proportion of neonates who received at least one course of systemic antibiotic therapy during the study period;AUR: defined as the number of antibiotic days per 1,000 patient-days.

#### Balancing measures

2.7.2

Incidence of LOS: the number of sepsis cases diagnosed ≥72 h after birth based on positive blood cultures and/or compatible clinical syndrome, divided by the total number of NICU admissions during the same period and expressed as a percentage;All-cause in-hospital NICU mortality;Antibiotic re-initiation rate: re-initiation of systemic antibiotics within 3 days after antibiotic discontinuation.

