### Statistical analysis

2.9

To rigorously evaluate whether the QI intervention achieves its intended goals, complementary analytical approaches will be used to establish a coherent chain of evidence. Statistical process control charts (*P*-charts) will first be used to monitor temporal variation in antibiotic use and to distinguish common-cause variation from special-cause variation potentially associated with the intervention. Special-cause variation observed after implementation will be interpreted as process-level evidence supporting intervention-associated change, particularly when accompanied by improved protocol adherence. Segmented regression ITS analysis will then be used to provide formal statistical inference by estimating the pre-intervention baseline trend, the immediate post-intervention level change, and the change in monthly trend during the intervention period. The overall effectiveness of the QI project will be assessed by integrating primary outcomes, process measures, and balancing measures. The intervention will be considered to have achieved its intended goals if reductions in the antibiotic use rate and/or AUR are observed, accompanied by improved protocol adherence, without concurrent increases in the incidence of late-onset sepsis, in-hospital mortality, or the antibiotic re-initiation rate.

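### Non-fatal sepsis diagnosed before 72 h in an infant not started on antibiotics is counted by no balancing measure, so the safety conclusion does not cover it

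*Protocol article*

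**What the plan says.** Module 2 (section 2.6.2) sets common criteria for starting antibiotics for suspected EOS. On maternal risk factors it says: "These factors are considered to increase EOS risk but do not independently constitute absolute indications for empirical antibiotic therapy". On laboratory markers it says: "Abnormality in a single parameter alone does not constitute sufficient justification for initiating or prolonging antibiotic therapy". High-risk preterm infants remain an indication, severe clinical manifestations remain absolute indications, and other nonspecific signs call for integrated assessment.

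Section 2.7.2 lists three balancing measures:

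- "Incidence of LOS: the number of sepsis cases diagnosed ≥72 h after birth", on the basis of culture or a compatible clinical syndrome, per NICU admission;
- "All-cause in-hospital NICU mortality";
- "Antibiotic re-initiation rate: re-initiation of systemic antibiotics within 3 days after antibiotic discontinuation".

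The success rule in section 2.9 asks for lower antibiotic use and better adherence, "without concurrent increases in the incidence of late-onset sepsis, in-hospital mortality, or the antibiotic re-initiation rate". The outcome data in section 2.8.1 include the dates and diagnostic basis of LOS, deaths with their causes, and re-initiations; EOS is not an outcome item. Section 2.6.3 refers to Supplementary Table S2 for EOS diagnostic criteria, but no outcome uses them.

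The abstract states an aim of safely reducing unnecessary exposure, and the Discussion describes the combined set of measures as a comprehensive assessment of effectiveness and safety.

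**The concern.** The bundle acts at two points: whether antibiotics are started (Module 2) and whether they are continued (Module 3). Stopping too early has a non-fatal indicator, re-initiation within 3 days. Not starting an infant who proves to have EOS has none while the diagnosis falls before 72 h. Yet the first primary outcome, the antibiotic use rate, can fall only if fewer infants are started.

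The plan thus credits fewer starts as benefit without a non-fatal measure of the corresponding early harm. Followed exactly, the success rule could be met while treatment of true EOS was being delayed, and the programme could then be offered to similar regions as safe. An analysis plan would not normally close this gap, because the article itself fixes the balancing measures, the outcome data and the success rule.

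**Working it through.** The plan states no figure on this point, so there is none to reproduce. The main check is to apply the three definitions in section 2.7.2 to each course an infant might take.

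| Course of the infant | LOS | Re-initiation | Mortality |
|---|---|---|---|
| Not started; sepsis diagnosed before 72 h; survives | no (too early) | no (nothing was stopped) | no |
| Not started; sepsis diagnosed before 72 h; dies in hospital | no | no | yes |
| Not started; sepsis first diagnosed at 72 h or later; survives | yes | no | no |
| Started, stopped, restarted within 3 days (no LOS diagnosis); survives | no | yes | no |

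The first row is counted nowhere as harm. Once that infant is treated, the treatment adds to the primary outcomes as antibiotic use, but it is not flagged as a safety event.

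The next question is whether mortality could act as a proxy. This is an illustration only: a plain comparison of two 12-month periods, not the planned interrupted time series.

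*From the documents.* Table 1 (2024): 862 + 524 + 395 + 872 + 484 = 3,137 admissions a year, used for each period.

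*Assumed, because the documents give no rates.* EOS 0.1% to 1.0% of admissions; a doubling as the harm; case fatality 5% to 15%; baseline mortality 0.5% to 1.0% for power and 0.5% to 2% for the chance threshold; two-sided 5% test.

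*Chance variation in deaths.* The year-to-year difference that exceeds chance is about 1.96 × √(2 × deaths per year):

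- 0.5%: 15.7 deaths, 1.96 × √31.4 ≈ 11.0
- 1%: 31.4 deaths, 1.96 × √62.7 ≈ 15.5
- 2%: 62.7 deaths, 1.96 × √125.5 ≈ 22.0

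*Power.* Φ(|p₂ − p₁| / SE − 1.96), with SE = √{[p₁(1 − p₁) + p₂(1 − p₂)] / 3,137}. For EOS going from 0.1% to 0.2%: SE = √[(0.000999 + 0.001996) / 3,137] = 0.000977, and Φ(1.02 − 1.96) ≈ 0.17.

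| Assumed EOS rate, doubled | EOS cases per year | Power if EOS is counted | Extra deaths (5% to 15% fatality) | Power through mortality |
|---|---|---|---|---|
| 0.1% | 3.1 → 6.3 | 17% | 0.16 to 0.47 | about 3% |
| 0.3% | 9.4 → 18.8 | 43% | 0.47 to 1.41 | 3% to 4% |
| 0.5% | 15.7 → 31.4 | 63% | 0.78 to 2.35 | 3% to 6% |
| 1.0% | 31.4 → 62.7 | 90% | 1.57 to 4.71 | 4% to 12% |

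With no change at all, this test would show a significant rise 2.5% of the time, so mortality carries almost no signal. Counting EOS directly does better, but at the lower rates it would still often miss a doubling.

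**The case against.** Several points on the other side are sound and limit the finding.

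- A reader might infer that EOS in any infant from whom antibiotics are withheld goes uncounted unless the infant dies. LOS is defined by time of diagnosis, so a survivor first diagnosed at 72 h or later does count. The gap is confined to diagnosis before 72 h.
- A reader might call this the programme's main new risk. The documents do not rank harms, and the bundle also mandates stopping.
- The narrowing of starts should not be overstated. Maternal factors are said not to be absolute indications on their own, and high-risk preterm and severely ill infants are still treated. Those not started are therefore selected for lower risk. Figure 2, the operative pathway, is not shown.
- From "Documentation will be mandatory for all empirical antibiotic initiations" a reader might infer that a decision to withhold need not be recorded. The sentence does not say only, and the pathway is described as mandatory in all participating NICUs.
- Such cases are not lost to the data. The registry form records the date and indication for initiation and blood-culture dates and results, and causes of death are collected, so a fatal EOS case could be identified individually. The gap lies in the declared outcomes and the success rule, not in data capture.
- A small count fits poorly in a no-increase rule. If the subset averaged an assumed 2 cases a year with no true change, the second year would exceed the first about 40% of the time: (1 − 0.207) / 2 ≈ 0.40, where 0.207 is the Poisson probability of equal counts.

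The last point shapes the fix. None of them gives the case in the first row of the table above a place among the safety measures.

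**Conclusion.** The point holds in a limited form. None of the balancing measures in section 2.7.2, and none of the safety conditions in section 2.9, counts non-fatal sepsis diagnosed before 72 h of age in an infant not started on antibiotics. The claims of safe reduction and comprehensive safety assessment therefore do not extend to this harm. That follows from the definitions alone and needs no assumed rate.

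Its size cannot be fixed from the documents. Total EOS would be about 3 to 31 cases a year at the assumed 1 to 10 per 1,000 admissions. The uncounted cases are an unknown subset of these, so the range must not be read as a number of missed infants. The power figures are likewise illustrative. The primary outcomes and the time-series analysis are unaffected, and nothing here shows that the pathway is unsafe.

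**What to change.** 1. **Section 2.7.2.** Add EOS incidence as a balancing measure: sepsis diagnosed less than 72 h after birth by the Supplementary Table S2 criteria, per NICU admission, with culture-positive and clinical cases shown separately. Show infants not on antibiotics at onset as a subset.
2. **Section 2.8.1.** Add the date and diagnostic basis of EOS to the outcome data, for both the 2025 baseline and the intervention period.
3. **Monthly meeting.** Review each case in the subset individually.
4. **Section 2.9.** State that the safety judgement also considers EOS incidence, reported as an estimate with a 95% confidence interval together with the case review, and that absence of a significant increase is not taken as proof of safety. The count should not be a bare no-increase condition.

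The subset is better defined by antibiotic status at onset than by a minimum delay after admission, which would miss infants who deteriorate early.

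The cost is small: a wording change and a variable built largely from items the centres already record. Counts will be low and intervals wide. Indication and culture results are listed as process data, drawn mainly from the registry form, so 2025 may need one further extraction from the electronic records. This changes measurement only; no treatment rule is altered.
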